## Methods

### Study design

A randomized controlled trial study design will be used (registered at the Dutch Trial Register; Trial ID, NTR5775). After providing informed consent, participant dyads (caregiver and a person with dementia) will be randomly assigned to an intervention or a control group. In the intervention group, participant dyads will take part in the training program (entitled “More at Home with Dementia”), while in the control group, participants will receive care as usual. Data will then be collected at three points: at baseline and during meetings at 3 and 6 months after the intervention. Additionally, information on the use of care and health facilities will be collected by telephone after 6 and 18 weeks. People who drop out of the intervention or control group will be contacted at regular times by phone to request information on the date of admission to a nursing home or death, as applicable.

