#### Instruments used to assess the secondary outcomes in caregivers

*CarerQol - visual analog scale (VAS).* For the VAS, 0 equals completely unhappy and 10 equals completely happy (29) (part of TOPICS-MDS).*Self-Rated Burden Scale - VAS.* This is a self-report measure of burden experienced in the caregiver role. Ratings are on a scale from 0 to 10, with higher scores indicating a higher burden (28) (part of TOPICS-MDS).*Objective caregiver burden.* This will be graded as the number of hours per week spent on caregiving (part of TOPICS-MDS).*RAND-36/short form (SF)-36.* This will be used to measure experienced health or health-related quality of life. The survey includes scales concerning physical functioning, role limitations due to physical health problems, bodily pain, general health perceptions, vitality, social functioning, role limitations due to emotional problems, and general mental health. Higher scores indicate better health [30] (part of TOPICS-MDS).*EuroQol-5 Dimensions + Cognition (EQ-5D + C).* This health instrument assesses quality of life on five dimensions: mobility, self-care, activities, pain and discomfort, anxiety and depressed mood, with an additional question about cognitive problems. All items are scored as no problems, some problems, or extreme problems (scored as 1, 2, or 3, respectively) [31, 32] (part of TOPICS-MDS).*Psychotropic drug use.* Medication use will be categorized into antipsychotics, anxiolytics, antidepressants, and hypnotics.*Center of Epidemiologic Studies-Depression (CES-D).* This instrument screens for depressive symptoms across 20 items. Each item is scored rarely, some or a little of the time, occasionally or a moderate amount of the time, or most or all the time (scored as 0, 1, 2, or 3, respectively). The maximum score is 60, and a score of 16 indicates depression [33].*Hospital Anxiety and Depression Scale-anxiety subscale (HADS-A).* This is a well-known 14 item scale that generates ordinal data to determine levels of anxiety or depression (7 items each relate to anxiety and depression). Each item on the questionnaire is scored from 0 to 3, and a person can score from 0 to 21 on the anxiety subscale, with higher scores indicating more symptoms [34].*Perseverance Time.* This is defined as how long the caregiver believes that he or she will be able to persevere in their current state provided the situation remains stable. Perseverance time will be categorized as follows, based on earlier research [35, 36]: (1) less than a week; (2) more than a week but less than a month; (3) more than a month but less than six months; (4) more than six months but less than a year; (5) more than a year but less than two years; or (6) more than two years.

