
#### Instruments used to assess the secondary outcomes in people with dementia

*The 12-item neuropsychiatric Inventory (NPI).* The main outcome of interest in the dementia group will be the NPI score. This is an informant-rated measure of the frequency and severity of neuropsychiatric symptoms, such as agitation, psychosis, depression and apathy in people with dementia, collected by interview with the caregiver. Higher scores indicate more severe neuropsychiatric symptoms [37].*Functional status.* We will assess this with an adapted version of the Katz Index of Independence of Activities for Daily Living (ADLs) and instrumental activities of daily living (IADLs), supplemented with a question concerning mobility (i.e., Katz-15; part of TOPICS-MDS). Caregivers will be asked if assistance is needed for six basic functions (e.g., bathing and dressing) and eight instrumental functions (e.g., telephoning and food preparation). Scores are binary (0 = independent, 1 = dependent), resulting in a potential total score between 0 and 15, with a higher score indicating a higher level of dependency [38].*Resource utilization.* Medical facility use and nursing home admission will be recorded from a week before baseline assessment and throughout the follow-up period (part of TOPIC-MDS). Use of services, such as home care, day care, and visits by case managers in the week before assessment will be recorded at baseline and at three and six months.*The Dementia Quality of Life Instrument (DQI).* This tool will be used to assess the quality of life of the people with dementia. It covers five health domains (i.e., memory, orientation, dependency, social activities, and mood); derived from the EQ-5D, it is effective at measuring quality of life in dementia of mild to moderate severity [39].*The Cohen-Mansfield Agitation Inventory-Community (CMAI-C) scale.* This is an informant-rated measure of the frequency of agitated behavior in people with dementia. Results are collected through interview with the caregiver and the score can range from 29 to 203, with higher scores indicating agitation that is more frequent [40].*The Geriatric Deterioration Scale (GDS).* This scale will be used to classify people with dementia based on the relative severity of their cognitive impairment and their functional status (range from 1 to 7), with higher scores indicating more severe dementia [41].

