#### Outcome analysis

For the primary outcome, the change in the CarerQol-7D score from baseline to 3 months, a linear regression model will be developed to test the response variable for differences between the intervention and control groups, adjusting for the baseline outcome scores. We will perform a primary intention-to-treat analysis for the primary equation, which will be complemented with a secondary per-protocol analysis. The intention-to-treat population will include all information from participants randomized to each treatment arm, whereas the per-protocol population will only include information about those who completed the program to which they were allocated.

For the secondary outcome variables, multilevel analyses will be used to account for the dependency of the repeated measurements. A restricted, iterative, generalized least-squares algorithm will be used to estimate the regression coefficients, while the Wald test will be used to obtain *P* values for each regression coefficient. Linear or binary multilevel analysis will be conducted depending on the outcome measure. Subgroup analyses will be performed to assess the heterogeneity of treatment effects.

Assumptions of the normality and homogeneity of variance in the linear regression models will be assessed by inspecting normal probability plots and plots of standardized residuals compared with predicted values. If assumptions are not met, variables will be transformed to comply with the assumptions. If this does not yield acceptable distributions, variables will be dichotomized or we will use non-parametric statistical analyses. All statistical tests will be two-sided and will be required to meet the 5% significance criterion.

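### The linear or binary multilevel models fitted by iterative generalised least squares suit neither the six-category perseverance time nor the binary secondary outcomes well

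*Protocol article*

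**What the plan says.** The Outcome analysis section of the protocol article assigns all secondary outcomes to multilevel models because the measurements are repeated. On estimation it says "A restricted, iterative, generalized least-squares algorithm will be used to estimate the regression coefficients", with Wald tests for the coefficients. On the model family it says "Linear or binary multilevel analysis will be conducted depending on the outcome measure".

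The same section then gives a fallback tied to residual checks of the linear models. Variables are first transformed and, if that does not help, "variables will be dichotomized or we will use non-parametric statistical analyses".

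The section on instruments for caregivers' secondary outcomes says "Perseverance time will be categorized as follows, based on earlier research". The scale runs from "1) less than a week; (2) more than a week but less than a month" up to more than two years, in six ordered categories. The same section lists psychotropic drug use by drug class, an outcome most naturally coded as use or no use.

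**The concern.** Two stated choices sit badly with outcomes that the article itself lists.

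- **Perseverance time.** The bottom category spans days and the upper ones span a year or more. A linear model on scores 1 to 6 treats every step as equal. A binary model merges categories and discards ordering. An ordinal model is not among the named families. The fallback is reached only after residuals have been inspected, although the scale type is known now. No monotone transformation turns six categories into a continuous variable.
- **Binary outcomes.** RIGLS is a least-squares algorithm. It handles a binary multilevel model only by linearising it, through marginal or penalised quasi-likelihood (MQL or PQL) of first or second order. With two or three measurements per person, the first-order versions are known to shrink the subject-specific coefficient.

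At stake are precision for perseverance time, and the size and meaning of the odds ratios reported for binary secondary outcomes.

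**Working it through.** **The plan's own figure.** The sample size section gives a standardised effect of 0.5, significance 0.05, power 0.8, 10% attrition and 144 dyads. A two-sided two-sample t-test needs 64 per arm; 64/0.9 = 71.1, rounded up to 72, and 2 × 72 = 144. The figure reproduces and is not in dispute. After attrition, 144 × 0.9 ≈ 130 dyads remain, 65 per arm.

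The article gives no category distribution, intraclass correlation or odds ratio. Those below are assumptions, shown as ranges.

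**1. Dichotomising perseverance time.** With category probabilities p_k and a cut at cumulative probability c, the information kept relative to a proportional-odds analysis is 3c(1 − c) / (1 − Σp_k³).

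| Assumed distribution, shortest to longest | 1 − Σp³ | Best cut c | 3c(1 − c) | Kept at best cut | Kept at worst cut |
|---|---|---|---|---|---|
| Six equal categories | 0.972 | 0.50 | 0.75 | 0.77 | 0.43 |
| Skewed: 0.02, 0.05, 0.13, 0.20, 0.25, 0.35 | 0.931 | 0.40 | 0.72 | 0.77 | 0.06 |
| Ceiling: 0.01, 0.02, 0.07, 0.10, 0.20, 0.60 | 0.775 | 0.40 | 0.72 | 0.93 | 0.04 |
| Middle: 0.05, 0.10, 0.25, 0.30, 0.20, 0.10 | 0.947 | 0.40 | 0.72 | 0.76 | 0.15 |

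The loss at the best cut is 1 − 0.93 = 7% to 1 − 0.76 = 24%. For this outcome, that is like losing about 9 to 31 of 130 dyads (0.07 × 130 and 0.24 × 130). A poor cut loses far more.

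**2. Scoring perseverance time linearly.** The check simulated 65 per arm at a single time point, with a cumulative log odds ratio of 0.9 and 4,000 replicates. It compared a t-test on scores 1 to 6 with a rank test.

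| Distribution | Power, linear scores | Power, rank test | Type I error, linear scores |
|---|---|---|---|
| Equal | 0.81 | 0.81 | 0.047 |
| Skewed | 0.75 | 0.79 | 0.049 |
| Ceiling | 0.59 | 0.67 | 0.051 |

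Linear scoring is valid as a test. It costs 0 to 8 points of power, most when many caregivers choose the top category.

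**3. Binary outcomes.** The check simulated a random-intercept logistic model with 130 dyads, 2 or 3 measurements and a true subject-specific log odds ratio of 1.0. The same arm effect applied at each measurement. The between-person variance is s² = ICC/(1 − ICC) × π²/3, and the approximate marginal log odds ratio is 1/√(1 + 0.346 s²). Entries are mean estimates over 300 replicates (150 for maximum likelihood, with 25-point quadrature); ranges cover 2 and 3 measurements.

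| Latent ICC | s² | RIGLS, first-order MQL | RIGLS, first-order PQL | Maximum likelihood | Marginal value |
|---|---|---|---|---|---|
| 0.3 | 1.41 | 0.79–0.80 | 0.82–0.83 | 1.00–1.04 | 0.82 |
| 0.5 | 3.29 | 0.65 | 0.69–0.73 | 1.01–1.04 | 0.68 |
| 0.7 | 7.68 | 0.48–0.49 | 0.53–0.60 | 0.97 | 0.52 |

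First-order shrinkage is therefore 17–21% at ICC 0.3, 27–35% at 0.5 and 40–52% at 0.7. Maximum likelihood stays within about 4% of the truth. Second-order PQL was not simulated.

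**The case against.** The strongest reply is that these are modest efficiency points on secondary outcomes, in a condensed article whose analysis plan is not shown. Much of that stands. Linear scoring of perseverance time is valid and loses nothing under an even distribution. The linearisation may well be specified elsewhere, and the article never selects a first-order form. What the reply does not remove is that the article itself names the model families and the algorithm, so these are stated choices and not gaps.

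Four stronger readings are tempting, and the document does not support them.

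- **That secondary outcomes may be analysed in no other way.** The fallback allows transformation and non-parametric analysis. It is conditional on failed linear-model checks, but it exists.
- **That the plan biases binary results into false negatives.** First-order MQL lands close to the marginal log odds ratio, which GEE also targets. The gap is largely one between two effect measures, and the Wald test is not invalid for that reason. The harm is a coefficient read as subject-specific when it is not.
- **That dated admissions call for a competing-risk analysis.** Under Study design, dropouts are contacted to "request information on the date of admission to a nursing home or death, as applicable". For everyone else the instruments section says only "Medical facility use and nursing home admission will be recorded from a week before baseline assessment and throughout the follow-up period", with no mention of dates. No outcome list names time to admission, and admission by 6 months can be analysed as binary.
- **That secondary comparisons, including the neuropsychiatric inventory, ignore baseline.** The article is silent on this. Baseline is one of the repeated measurements and can enter the model as such.

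**Conclusion.** The point holds as a limited one about secondary outcomes. For perseverance time, neither named model family fits a scale whose ordinal nature is known beforehand. The cost is 0 to 8 points of power with linear scores, or 7 to 24% of the information with the best dichotomy and more with others. For binary outcomes, RIGLS is a weak choice with two or three measurements per person. If a first-order linearisation is used, the subject-specific log odds ratio is understated by roughly a fifth at a latent ICC of 0.3 and by about a third at 0.5.

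All these sizes rest on assumed distributions, effect sizes and correlations, and the binary figures also on a linearisation that the article does not state. The perseverance-time power check used one time point, not the full repeated-measures model. The primary analysis of CarerQol-7D and the 144 dyads are untouched.

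**What to change.** In the Outcome analysis section:

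1. Prespecify a cumulative-logit mixed model with a random intercept for perseverance time, in place of linear scoring or dichotomising.
2. Fit binary multilevel models by maximum likelihood with adaptive quadrature in place of RIGLS. Alternatively, use GEE and label the result as a marginal odds ratio. GEE would need to be combined with the multiple imputation already planned if data are missing at random and not completely at random.
3. Keep RIGLS for the continuous secondary outcomes, where this point does not arise.

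The cost is a proportional-odds assumption to check and slightly more analysis work in standard software. No new data, visits or participants are needed.

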Developing effective interventions that target caregivers can benefit both the caregiver themselves and the person for whom they care. There is extensive literature on this issue, but heterogeneity of interventions and outcomes make it difficult to identify the most effective and relevant interventions. Most reviews have only indicated mild to moderate effect sizes with common interventions, while some subgroup analyses have shown stronger positive effects [10–21]. Interventions in these subgroups have tended to incorporate the following: group training, social support, cognitive interventions, intensive programs, multi-model programs with multiple components, programs that focus on the caregiver/patient dyad, caregiver training, caregiver family involvement, adapting to caregivers’ needs, and providing psychological education. By contrast, reviews on the effects of respite care have shown that this intervention generates no benefits [22, 23]. In Australia, a residential caregiver training program has been developed that incorporates most of the components shown to be effective in these reviews. This showed promise, effectively delaying nursing home admission, lowering mortality, reducing psychological morbidity in caregivers, and lowering care costs [9, 24–26]. This program is now being investigated in another study (entitled the “Going to Stay at Home” program), for which a protocol was recently published [27].

In the Netherlands, dementia is typically diagnosed in geriatric outpatient clinics, by general practitioners (GPs), or by elderly care physicians. Following diagnosis, patients are referred to a case manager specializing in dementia, who supports the caregiver and gives advice concerning home care, day care, and nursing home admission. However, there are significant local differences regarding the availability of and the accessibility to these health services. Moreover, the Australian interventions were delivered in nursing home or hospital settings, and we thought it would be interesting to known whether such services can be delivered in non-medical residential settings.

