In this study, we will adapt a caregiver training program for use in informal non-medical settings in the Dutch health care system and determine the effectiveness of that program based on several key outcomes. The primary outcome will be the caregiver-related quality of life after 3 months. The secondary outcomes will be two-fold. First, for the caregiver, we will assess the quality of life course, caregiver burden, health, care utilization, psychotropic medication use, depressive and anxiety symptoms, and perseverance time. Second, for people with dementia, we will assess the courses of neuropsychiatric symptoms, activities of daily living, utilization of care, costs of care, quality of life, agitation, use of psychotropic medication, and severity of dementia.

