#### Program for caregivers

The caregivers will attend 14 psycho-educational sessions. These will be delivered in an informal setting by a psychologist, a physiotherapist, an occupational therapist, an elderly care physician, a speech therapist, a dietician, and a social worker. Sessions will include didactic elements, group work, modeling, and role play, as follows:*Combating social isolation.* Participants will be stimulated to share their experiences and to explore available social contacts, support and needs. An open and supportive relationship can be established between caregivers during the intervention and subsequent meetings.*Medical aspects of dementia.* Relevant information will be provided about the types of dementia and associated changes in behavior, as well as accompanying symptoms like apraxia and aphasia. Frequently occurring complications like delirium and depression will be explained.*Planning for the future.* The need to plan for future emergencies and unforeseen events will be discussed, including driving, legal and financial matters, and advance care directives. The issues will be explored during the sessions, but participants will be advised to explore them further at home, preferably with their partner, and if necessary with the help of relatives or professionals.*Re-rolling.* This session will explore issues regarding changes in the roles and responsibilities of the caregiver and the person with dementia. Caregivers will be assisted in considering ways to take over tasks from the people with dementia while preserving their dignity. Attention will then be paid to how to deal with new responsibilities.*Reminiscence and orientation.* Caregivers will be provided with information on techniques that encourage reminiscence (e.g., life history book, music, objects representing notable events) and orientation to the environment and reality (e.g., signs and clocks designed for people with dementia).*Communication.* Information will be given about aphasia and how it affects communication, together with management strategies. Attention will be paid to problems with swallowing.*Assertion.* It will be important to provide training about assertive, non-assertive, and aggressive behaviors, and to provide strategies to cope with criticism. The rights of caregivers should be emphasized and observed, and their needs should be heard and met.*Therapeutic use of activities.* We will identify meaningful and enjoyable activities that are increasingly difficult for the people with dementia to perform. Caregivers will be taught a method of activity analysis that will enable them to break these activities down into component steps and modify or eliminate steps that cannot be completed.*Organization of work and safety in the home.* This session will focus on simplifying, prioritizing, and using outside assistance to achieve a better balance between work and leisure. Attention will be paid to safety at home.*Nursing skills.* Issues associated with dementia will be discussed, such as incontinence, personal care, medication, and mobility. Caregivers will be educated about how to give personal care to a nursing standard, focusing on washing, assistance with dressing, assistance with rising from a chair or bed, and managing incontinence.*Fitness.* The benefits of exercise for both the caregiver and the person with dementia will be emphasized. If possible, exercises or walks will be included in the program. In case of disability, alternatives to walking will be discussed.*Nutrition.* Attention will be paid to the changes in diet, food intake, food preferences, and nutritional needs of people with dementia. Caregivers will be given advice about how to deal with these issues and about how to improve the eating experience.*Self-care.* Caregivers will be given the opportunity to identify their support needs. Attention will also be paid to stress management and relaxation techniques.*Using community services.* Information will be distributed about the many support services that are available (e.g., day care and support at home) and about how to access them. Special emphasis will be given to the financial costs of these services for the couple.

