### Outcome measures

The effectiveness of the program will be assessed based on the following primary and secondary outcomes. The primary outcome will be the caregiver-related quality of life after 3 months. The secondary outcomes will be subdivided to those in the caregiver groups and those in the dementia groups. In the caregiver groups, we will assess quality of life, caregiver burden, experienced health, care utilization, psychotropic medication use, depressive and anxiety symptoms, and perseverance time. In the dementia groups, we will assess the courses of neuropsychiatric symptoms, activities of daily living, utilization of care, costs of care, quality of life, agitation, psychotropic medication use, and dementia severity. Secondary outcome variables will be measured at baseline and after 3 and 6 months and compared between the intervention and control groups.

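### The fallback rule for non-normal variables makes no exception for costs of care, so the cost comparison is likely to move off the difference in mean cost

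*Protocol article*

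**What the plan says.** The Outcome measures section lists these among the outcomes in people with dementia: "utilization of care, costs of care, quality of life, agitation, psychotropic medication use, and dementia severity". The aims at the end of the Background repeat costs of care. The plan is to compare the arms on them: "Secondary outcome variables will be measured at baseline and after 3 and 6 months and compared between the intervention and control groups".

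The Outcome analysis section gives secondary outcomes one modelling route: "For the secondary outcome variables, multilevel analyses will be used to account for the dependency of the repeated measurements", and "Linear or binary multilevel analysis will be conducted depending on the outcome measure". It then says how the assumptions of normality and homogeneous variance will be inspected. Variables that fail are transformed first, and after that: "If this does not yield acceptable distributions, variables will be dichotomized or we will use non-parametric statistical analyses". The section does not single out costs, and it names no method that keeps the mean as the target, such as a bootstrap of the mean, a generalized linear model or a back-transformation.

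**The concern.** A statement about care costs is a statement about total spending, and total spending is the number of people times the arithmetic mean. The rule leads elsewhere. A log transformation compares geometric means, dichotomising compares proportions above a cut-off, and a rank test compares the probability that one person costs more than another. Deciding in advance which of the three to use would not help, because the quantity estimated is the problem.

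This matters here because lower cost is one of the earlier findings that motivate the replication; the Background describes the Australian program as "effectively delaying nursing home admission, lowering mortality, reducing psychological morbidity in caregivers, and lowering care costs". The article's own content also gives a reason why the bulk and the tail of the cost distribution might move differently. The earlier program delayed admissions, which are expensive and few. One caregiver session promotes use of services: "Information will be distributed about the many support services that are available". More day care and home support would raise routine cost for many dyads, while fewer admissions would lower very high cost for a few. Logs, ranks and cut-offs give most weight to the former.

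**Working it through.** **Inputs from the article.** 144 dyads, equally divided, 10% attrition (Sample size calculation). The size reproduces: a two-sample t-test with effect size 0.5, two-sided 5% and 80% power needs 64 per arm; 64/0.9 = 71.1, so 72 per arm and 144 in total. After attrition, 144 × 0.9 = 129.6, about 65 per arm. This point does not dispute the sample size; it sets the scale for the check.

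**Inputs assumed.** The article gives no cost, spread or admission figures. In arbitrary units, routine cost is log-normal with median 2 and log-SD 1 in the control arm. The program multiplies routine cost by a factor *u*. An admission adds 15 units, with probability *p*₀ (control) or *p*₁ (intervention).

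**Formula.** Mean cost = median × exp(1/2) + 15 × *p*. For *u* = 1.30, *p*₀ = 0.15, *p*₁ = 0.05:
- control: 2 × 1.6487 + 15 × 0.15 = 3.297 + 2.25 = 5.55
- intervention: 2.6 × 1.6487 + 15 × 0.05 = 4.287 + 0.75 = 5.04
- change in mean: 5.037/5.547 − 1 = −9.2%

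The geometric mean ratio, by numerical integration of E[log cost], is 1.03. The share above the pooled median rises from 48% to 52%, and the probability that an intervention dyad costs more than a control dyad is 0.51. All three contrasts point to slightly higher cost while the mean falls.

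The last two columns come from 20,000 simulated trials per row at 65 per arm: how often a t-test on log cost is significant for higher cost, and how often a Welch test on raw cost is significant for lower cost.

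| Routine cost | Admissions | Change in mean | Change in geometric mean | Log test: costlier | Mean test: cheaper |
|---|---|---|---|---|---|
| +30% | 15% to 5% | −9.2% | +3.3% | 3.3% | 6.9% |
| +20% | 12% to 6% | −4.7% | +4.2% | 4.0% | 4.1% |
| +20% | 10% to 5% | −1.9% | +6.7% | 5.1% | 3.2% |
| +25% | 12% to 4% | −7.4% | +4.1% | 3.9% | 5.5% |
| +20% | 15% to 5% | −15.2% | −4.4% | 1.5% | 11.8% |

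The signs differ in the first four rows. In the fifth they agree, but the log scale shows less than a third of the saving.

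**Where the signs agree.** With routine cost raised by only 10%, mean and geometric mean both fall: −21% and −12% for 15% to 5%; −11% and −4% for 12% to 6%; −9% and −2% for 10% to 5%. On a grid of 48 assumed combinations (routine cost +0% to +40%, six admission pairs), the signs differed in 12.

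**A second model.** If cost is log-normal in both arms, mean = median × exp(σ²/2). With equal log-SD the mean ratio equals the geometric mean ratio, and the signs always agree. With median ratio *r* and control log-SD σ₀, they differ once the intervention log-SD exceeds √(σ₀² − 2 ln *r*). For *r* = 0.8 and σ₀ = 1 that is √(1 + 0.446) = 1.20. A change in the tail relative to the bulk is therefore required.

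**The case against.** The strongest reply is that a generic fallback is being read as a cost analysis. The article gives no unit prices, perspective or definition of total cost, and its Abstract lists use of health facilities but not costs. An economic plan may exist, and its absence from a journal article is no fault. That stands, and the point does not rest on it. It rests on the published rule, which covers secondary variables without exception.

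Second, the rule's wording refers to linear regression models, whereas secondary outcomes get multilevel models, and the first-line linear model does estimate a mean difference. Both observations are fair. But no other rule is given for a continuous secondary outcome, and costs that include admissions are likely, though not certain, to fail the checks.

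Third, it is too much to say that nothing under the rule could recover the mean. A bootstrap of the mean is itself non-parametric, and a log model can be back-transformed. The rule does not forbid either, but it names neither, and its ordinary reading is a rank test or a cut-off.

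A reader might infer that the trial will report a saving as an extra cost. The documents do not support that. Reversal needs opposing movements whose sizes the article does not give, and in the first row of the table even the observed mean difference has the wrong sign in about 32% of simulated trials. The likelier harm is an understated difference or an uninterpretable null.

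**Conclusion.** The point holds as a mismatch between a stated rule and the quantity of interest. If costs fail the checks, the plan as written probably replaces the difference in mean cost with a geometric-mean, cut-off or rank contrast. That contrast can understate a difference and can, under opposing movements of routine cost and admissions, differ in sign. All sizes rest on assumed distributions. In the cases shown, at about 65 per arm, the log test is significant for higher cost in roughly 1 to 5% of trials, and a mean-based test detects the saving in roughly 3 to 12%, so most trials would be inconclusive either way. What is at stake is whether the estimate and interval describe mean cost. This concerns one secondary outcome; the CarerQol-7D analysis and the NPI as main secondary outcome are untouched.

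**What to change.** In the Outcome analysis section, add a sentence exempting costs of care from the transform, dichotomise or non-parametric rule. Estimate the between-arm difference in mean cost on the original scale, adjusted for baseline cost, with a bootstrap confidence interval, or use a generalized linear model with contrasts expressed as mean differences.

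State also which cost is meant. Under the resource utilization item, admissions and medical facility use are recorded throughout follow-up, but home care, day care and case-manager visits only for the week before the baseline, 3-month and 6-month assessments. The Study design section adds telephone collection of care use at 6 and 18 weeks. Either analyse cost over the periods actually recorded, or define a 6-month total and state how the one-week records and the two calls are extrapolated.

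The cost is a few sentences, some programming and an interval wider than on the log scale. No new data collection is needed, but a 6-month total would depend on the extrapolation and should be reported as such.
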